### Design

The design is a single-blind, randomized controlled trial (RCT) comparing two trauma-focused cognitive-behavioural treatment (with and without positive memories’ module) for female survivors of IPV and a wait-list condition (superiority trial). A multigroup design (3 groups) will be used with repeated measures with five levels (pretreatment, posttreatment and follow-ups of 3, 6 and 12 months) for the experimental groups and two levels (pre and post) for the control group. Consequently, the three treatment groups are as follows: (a) waiting list control group (WL), (b) cognitive-behavioural treatment (CBT), and (c) cognitive-behavioural treatment with a focus on positive memories (CBT-M +).

Assessors of treatment outcomes will be blinded to the experimental conditions. To avoid unplanned imbalances in the size of the three groups and a loss of statistical power, a block randomization procedure will be used.

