### Eligibility criteria

We adopt the WHO definition of IPV as ‘any behaviour within an intimate relationship that causes physical, psychological or sexual harm to those in the relationship’ [29]. Participants are eligible if they (1) are women; (2) are over 18 years old; (3) are proficient in the use of the Spanish language; (4) are or have been victims of IPV; (5) have experienced IPV at least one month before the start of the trial; (6) present symptoms of PTSD according to DSM-5 criteria as determined by the Global Assessment of Posttraumatic Stress Scale 5 (EGEP-5; in Spanish: Evaluación Global de Estrés Postraumático 5; Crespo et al. [30]); and (7) have voluntarily agreed to take part in the study.

Participants will be excluded if they (1) show suicide risk as assessed by item 9 (scores > 1) of the Spanish version of the Beck Depression Inventory II—BDI-II [31]; (2) present conditions that could prevent compliance with the treatment (namely, abuse of alcohol or drugs, cognitive impairment or illiteracy in Spanish); (3) have been diagnosed or suffer from psychotic disorders; and (4) have received trauma-focused treatment within the past 6 months.

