### Sample size

To determine the target sample size, we considered the effect sizes found in the literature (specifically, the overall effect size—omnibus—calculated in the meta-analysis by Arroyo et al. [5]), which ranges from 0.71 to 1.33. Considering an alpha of 0.05 and a statistical power level of 0.80, a minimum group size of 31 was established. Taking a conservative estimate of the expected dropout rate of 30%, a sample size of 45 women per group will be the target, indicating a total of 135 participants across the 3 experimental conditions (CBT, CBT-M + and WL control group).

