#### Primary outcomes

##### PTSD severity and diagnosis

The primary outcome is the change in the DSM-5 PTSD symptoms. These symptoms will be assessed with the Global Assessment of Posttraumatic Stress Scale 5 (EGEP-5; in Spanish: Evaluación Global de Estrés Postraumático - 5; Crespo et al. [30]), a self-reported measure that assesses the overall severity of PTSD symptoms and provides scores for the DSM-5 clusters for PTSD as well as PTSD diagnosis. The EGEP-5 shows high internal consistency for all severity symptom scales (ranging from 0.72 to 0.86) and for the total (0.91).

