In a second moment of the analysis of the changes over time, the changes between the pre, post and follow-ups will be analysed only for the two experimental groups. For this, an ANOVA will be applied for each of the outcome variables, including an intergroup factor (with two levels: CBT and CBT-M +) and an intrasubject or repeated measures factor, with five levels (i.e. pre, post, 3 months, 6 months and 12 months). In the application of these ANOVAs, the assumption of sphericity will be verified using the Mauchly test, and where appropriate, the Huynh-Feldt correction will be used. Likewise, ANCOVAs of one factor (type of treatment) will be performed for each outcome variable, using the value of the pretreatment evaluation as covariance.

To determine the differences between the two treatments, the intergroup differences and the interactions between time and type of treatment obtained in the different ANOVAs and ANCOVAs mentioned in the previous point will be addressed.

In all analyses, the Holm–Bonferroni correction will be used to adjust the level of significance for multiple comparisons.

To establish the clinical significance of the changes obtained, *χ*^2^ tests will be used considering the data relative to those variables that present a cut-off point capable of discriminating the clinical improvement of the participants. Likewise, the relative risk of presenting problems of one experimental group with respect to the other at different times of measurement will be calculated. In addition, the McNemar related proportions will be calculated to verify if the percentage of problems is the same or different in the pretreatment and in the different subsequent measurement moments, and the Jacobson-Truax method will be applied by calculating the index of reliable change. This analysis will be supplemented by the calculation of the effect size of each variable.

In the specific analysis of the reabuse or revictimization variables, it is expected that the scores show high asymmetry and kurtosis, so they will be recoded as dichotomous variables (presence vs. absence for each type of violence or abuse) in accordance with the procedure described by Johnson et al. [12].

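### One-year effects and clinical significance are listed under efficacy but rest partly on within-arm change from pretreatment, which cannot separate treatment from natural recovery or regression to the mean

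*Protocol article*

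**What the plan says.** **Selection and outcome.** Under Eligibility criteria, women must "present symptoms of PTSD according to DSM-5 criteria as determined by the Global Assessment of Posttraumatic Stress Scale 5". The section on PTSD severity and diagnosis names the same scale for the primary outcome: "These symptoms will be assessed with the Global Assessment of Posttraumatic Stress Scale 5". It adds that the scale also yields the PTSD diagnosis.

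**Control.** The Design section gives five measurement times for the two treatment arms but "two levels (pre and post) for the control group". Under Procedure, wait-list women are re-evaluated after 2 months and then offered treatment. The follow-up analysis covers only CBT and CBT-M+.

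**Objectives.** The list introduced as determining efficacy has four items: CBT-M+ against wait-list, CBT-M+ against CBT, the effects of CBT-M+ over time up to 1 year, and the clinical significance of the changes that the treatment obtains.

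**Analysis of the last two items.** The Statistical analysis section plans a five-level repeated-measures ANOVA with a two-level group factor. For clinical significance it plans chi-square tests on variables with a cut-off and a relative risk between the treated arms: "the relative risk of presenting problems of one experimental group with respect to the other at different times of measurement will be calculated". It then adds "the McNemar related proportions will be calculated to verify if the percentage of problems is the same or different in the pretreatment" and at each later measurement, together with the Jacobson–Truax reliable change index. Holm–Bonferroni applies to all analyses.

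**The concern.** The third and fourth efficacy items are worded as effects of treatment, and the one-year item stands apart from the comparison with CBT. Part of the analysis that serves them is change from pretreatment within a treated arm. Women who enter because they score above a threshold on a scale will, on average, score lower when the same scale is repeated, and some recover without treatment. After about 2 months no untreated arm shows how much of the change that accounts for.

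PTSD diagnosis is the sharpest case. If nearly all women are positive at pretreatment because entry required it, they can move in one direction only, and McNemar then asks little more than whether some women fall below the threshold. A significant change from pretreatment to 12 months could be reported as one-year efficacy even if CBT-M+ did no better than CBT and had no lasting advantage over no treatment.

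**Working it through.** **Arm sizes.** The Sample size section states: "Considering an alpha of 0.05 and a statistical power level of 0.80, a minimum group size of 31 was established", from effect sizes "which ranges from 0.71 to 1.33". With the lower bound 0.71 and a two-sided test, n = 2 × ((1.96 + 0.84)/0.71)² = 31.1, in line with the stated 31. For 30% dropout, 31/0.70 = 44.3, so 45 per arm and 3 × 45 = 135. Hence 31 (retained) and 45 (randomised) bracket the women per arm in a within-arm test.

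**Step 1: changes needed for significance.** Assume all women have the diagnosis at pretreatment. No one can become a new case, so with k women falling below threshold the exact two-sided McNemar p is 2 × 0.5^k:
- k = 5: 0.0625
- k = 6: 0.031
- k = 7: 0.0156
- k = 8: 0.0078

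Unadjusted, 6 changes suffice: 6/45 = 13% or 6/31 = 19%. If the Holm family is the four tests of pretreatment against post, 3, 6 and 12 months (an assumption; the family is not stated), the smallest p must be at most 0.05/4 = 0.0125. That needs 8 changes: 8/45 = 18% or 8/31 = 26%.

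**Step 2: how many fall below with no true change.** Take a bivariate normal score with retest correlation r, a share p of screened women who qualify, and the screening score as baseline. With c = Φ⁻¹(1 − p), the fraction below the cut-off on retest is

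q = ∫ from c to ∞ of [φ(x)/p] × Φ((c − r·x)/√(1 − r²)) dx.

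For p = 0.5 this reduces to arccos(r)/π; at r = 0.80 it is 0.6435/3.1416 = 0.205. The protocol gives neither r nor p. It gives an internal consistency of 0.91 for the EGEP-5 total, used here only as an optimistic value for r.

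**Step 3: chance that one visit reaches significance.** This is P(X ≥ 6) or P(X ≥ 8) for X binomial(n, q).

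| Assumption | q | ≥6 of 31 | ≥6 of 45 | ≥8 of 31 | ≥8 of 45 |
|---|---|---|---|---|---|
| r 0.91, 70% qualify | 8.5% | 0.04 | 0.18 | 0.003 | 0.03 |
| r 0.80, 50% qualify | 20.5% | 0.63 | 0.92 | 0.29 | 0.73 |
| r 0.60, 30% qualify | 42.4% | 1.00 | 1.00 | 0.98 | 1.00 |
| Natural recovery of 20% alone | 20% | 0.61 | 0.91 | 0.27 | 0.70 |

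**Step 4: which planned analyses are exposed.** Exposed: McNemar from pretreatment, within-arm reliable change, and the time effect of the five-level ANOVA. Not exposed: the baseline-adjusted ANCOVA against wait-list at post, the group differences and time-by-treatment interactions for CBT-M+ against CBT, and chi-square tests and relative risks between arms. Regression and natural recovery are expected to be similar in randomised arms, so they cancel in those contrasts.

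**The case against.** The strongest reply is that the trial's comparative conclusions do not depend on McNemar. The clinical-significance paragraph opens with chi-square tests and a between-arm relative risk; McNemar is an addition whose stated purpose is only to check whether a proportion has changed. The randomised CBT arm stays in place to 12 months. The protocol nowhere says that a significant McNemar result will count as proof of efficacy. This stands, and it rules out four stronger readings that a reader might infer:

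- **That there is no control beyond 2 months.** Only the untreated control ends; CBT remains an active comparator throughout.
- **That clinical significance is judged only within arms.** Between-arm tests are planned at several times.
- **That remission against wait-list goes untested.** Chi-square tests are assigned to qualitative variables and are not limited to the treated arms. What is not named is a relative risk for that contrast.
- **That a significant result is to be expected in an ineffective arm.** The range above includes low probabilities, and the stated Holm–Bonferroni correction lowers them further.

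Two more limits apply. Screening and the initial evaluation are separate appointments. If the EGEP-5 is repeated at the second (not stated), some regression happens before baseline and fewer than 100% may be positive there. The one-direction argument also applies to PTSD diagnosis, not to every variable with a cut-off.

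The reply does not remove the placement of within-arm change under efficacy. Nor does multiplicity control help with it: the correction guards against chance findings, whereas with natural recovery the McNemar null hypothesis is false without any treatment effect.

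**Conclusion.** The point holds for the within-arm components. As worded, the one-year and clinical-significance objectives attribute to treatment a change that these analyses cannot attribute, in women chosen on the outcome scale and with no untreated arm after about 2 months.

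The size is not fixed by the protocol. Under the assumed retest correlations and qualifying shares, the chance of a significant McNemar result at one visit with no treatment effect runs from 0.04 to 1.00 at 31 per arm and from 0.18 to 1.00 at 45, unadjusted. With 8 changes required, it runs from 0.003 to 0.98 and from 0.03 to 1.00. All these figures assume that every woman is positive at pretreatment.

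The sample size and the randomised contrasts are untouched. This is a cheap improvement to what the trial may conclude, not a flaw in its main comparisons.

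**What to change.** 1. State that McNemar from pretreatment, within-arm reliable change and time effects are descriptive and are not evidence of efficacy. Do not use McNemar from pretreatment as a test on PTSD diagnosis.
2. Rest clinical significance on between-arm proportions of women below the cut-off and of women reliably changed. Extend the planned relative risk, with a confidence interval, to each treatment against wait-list at post, and keep it for CBT-M+ against CBT at post, 3, 6 and 12 months.
3. Reword the one-year objective as two parts: maintenance from post to 12 months, reported descriptively, and the CBT-M+ versus CBT difference over follow-up.

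All of this uses data already planned for collection and changes only the wording of the protocol and analysis plan. The price is a more modest one-year claim: durability and the difference between two active treatments, not one-year efficacy against no treatment.

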### Statistical analysis

For the graphic description of the flow of the participants throughout the protocol, the CONSORT diagram is used. The intention-to-treat (ITT) method will also be used. In the treatment of the missing values, it will be checked if the loss of data occurs completely at random using Little’s MCAR test, and then, the estimation of the missing values will follow the maximum likelihood method through the EM algorithm [73].

As a step prior to determining the effectiveness of the intervention programs, the homogeneity of the groups will be analysed, taking into account all the variables evaluated and using *χ*^2^ tests and ANOVAs according to the type of variables.

To determine if the treatment is better than the control group, one-factor (type of intervention) ANOVAs and ANCOVAs will be performed for each of the scores in the posttreatment (or second pre measure for the control group on the waiting list) of the continuous treatment outcome variables, using in the ANCOVAs the value of the pretreatment evaluation as covariance. In the case of ANOVAs, the DSM or Games-Howel tests will be used for post hoc analyses depending on whether the assumption of equality of variances is met. In the case of significant differences in the ANCOVAs, the groups will be analysed in pairs using new ANCOVAs. For those variables that do not adjust to normality, the corresponding nonparametric tests will be applied (i.e. Kruskal–Wallis and Mann–Whitney *U* for pairwise comparisons). For the qualitative variables, *χ*^2^tests will be used.

To determine the changes over time, the two basic moments will be analysed first (i.e. the changes from pretreatment to posttreatment or the second premeasure for the control group). Repeated-measures ANOVAs will be performed in a mixed design with an intergroup factor with three levels (the two treatments plus the control group) and an intrasubject factor (pre and post measures). In those variables that do not adjust to normality, the corresponding nonparametric tests will be applied (i.e. Friedman). Additionally, in this case, for the qualitative variables, *χ*^2^ tests will be used.

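### The only missing-data rule, a single EM fill, makes no exception for the yes/no outcomes, and it misclassifies missing women whichever way it is applied

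*Protocol article*

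**What the plan says.** All of the following is in the Protocol article.

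- **Missing data (Statistical analysis).** The approach is intention to treat. After Little's test, "the estimation of the missing values will follow the maximum likelihood method through the EM algorithm". No type of outcome is excepted.
- **Reabuse (Statistical analysis).** The scores are expected to be strongly skewed, "so they will be recoded as dichotomous variables (presence vs. absence for each type of violence or abuse". The recoding follows a procedure in a cited trial that the article does not reproduce.
- **Clinical significance (Statistical analysis).** Chi-square tests are run "considering the data relative to those variables that present a cut-off point capable of discriminating the clinical improvement of the participants". The relative risk of presenting problems, one treatment against the other, is calculated at each time point. McNemar comparisons with baseline are also planned.
- **Dropout.** The Sample size section inflates for 30% dropout and calls that figure conservative: "a sample size of 45 women per group will be the target". The Discussion names lower dropout as an aim of the new programme.

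The article does not say whether the fill comes before or after recoding, which filled value counts as presence, or how a woman with no assessment is classified on these outcomes.

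**The concern.** An EM fill replaces a missing score by its conditional mean. That is a prediction of the average and not a plausible individual score. When it is turned into yes/no, all the individual variation that decides who falls on which side has been removed.

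For a skewed abuse score, the predicted mean is a small positive number for nearly everyone, including women who would have scored zero. For a cut-off on a roughly symmetric score, the predictions bunch around the mean and fall mostly on one side.

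Reabuse and clinical significance are both named among the trial's aims. If one arm keeps more women under assessment, the misclassification differs between arms and can create or hide a difference.

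**Working it through.** **The plan's own figures.** With effect size 0.71 (lower end of the range given), two-sided alpha 0.05 and power 0.80, n per group = 2(1.96 + 0.842)² / 0.71² = 15.70 / 0.504 = 31.1. That agrees with the stated 31, or 32 if rounded up. Dropout: 31 / 0.70 = 44.3, so 45. If 30% of 45 had no assessment, that would be 13.5 women per arm.

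**Assumptions that are not in the document.** True reabuse 10–30%; baseline-to-follow-up correlation 0–0.6 for reabuse and 0.3–0.7 for cut-off scores; 30% missing completely at random; a fill equal to the regression prediction with no residual draw.

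**Reabuse: share of missing women coded as reabused** (simulation, 90 women in two arms)

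| Way of applying the rule | Coded present |
|---|---|
| Fill the score, presence = any value above 0 | about 80–99% |
| Fill the score, presence = 1 or more | roughly 13–69% |
| Recode to 0/1, fill, round at 0.5 | about 0–13% |

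The middle row depends heavily on how large the non-zero scores are; a count model with larger scores gives 31–95%. The other two rows are stable.

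**Effect of unequal missingness.** Reported rate = p(1 − d) + f·d, where p is the true rate, d the missing share and f the share of missing women coded present. Take p = 0.20 in both arms and, as an illustration, d = 0.15 against 0.30:

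- Fill, above 0 (f = 0.97): 0.170 + 0.146 = 32% against 0.140 + 0.291 = 43%.
- Fill, 1 or more (f = 0.40): 0.170 + 0.060 = 23% against 0.140 + 0.120 = 26%.
- Recode first (f = 0.02): 0.170 + 0.003 = 17% against 0.140 + 0.006 = 15%.

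The direction reverses between the first and last lines. In the first case a nominal 5% chi-square test rejects about 22–23% of the time with no true difference.

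**Cut-off outcomes: average rate.** For a standard normal score with cut-off c and correlation r, the true share above is 1 − Φ(c), but the share among filled women is 1 − Φ(c/r). For a true 30%, c = 0.524:

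- r = 0.3: filled share 0.040; overall 0.7 × 0.30 + 0.3 × 0.040 = 22% (23% simulated at this sample size).
- r = 0.5: filled share 0.147; overall 25%.
- r = 0.7: filled share 0.227; overall 28%.

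A true 70% moves to 72–77% in simulation. At 50% the average does not move.

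**Cut-off outcomes: test.** With 45 per arm, 30% missing in each, half truly above the cut-off, no true difference and arm in the fill model, the nominal 5% chi-square test rejects about 25%, 14% and 9% of the time at r = 0.3, 0.5 and 0.7. Repeated simulations range over 8–26%. By chance an arm's estimated mean lands just above or below the cut-off and takes most of that arm's filled women with it.

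If arm is left out of the fill model, rejection stays close to 5%, but a true difference is diluted. Suppose the arm means lie 0.71 SD apart, symmetrically about the cut-off. The true difference is 2Φ(0.355) − 1 = 28 points. Without arm, filled women add nothing: 0.7 × 27.7 = 19 points. With arm and r = 0.5, filled women differ by 2Φ(0.71) − 1 = 52 points, giving 19.4 + 0.3 × 52.2 = 35 points.

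**The case against.** A reader might infer that the plan will code almost every missing woman as reabused and so favour the arm with better retention. The document does not support that. It takes two choices the article does not make: filling the raw scores first, and counting any positive value as presence. Recoding first reverses the error. The order of the text makes filling first the more natural reading, but it is not stated.

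A reader might also take the 30% as the share of women with no outcome. It is a planning figure for dropout, labelled conservative. The adherence analysis counts dropout by treatment session, and under intention to treat a woman who stops treatment may still be assessed. The article gives no dropout rates by arm; 15% against 30% is only an illustration.

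The cited reabuse procedure, the full protocol or an analysis plan may hold further detail, and an article need not carry all of it. That would defeat a complaint that something is missing. It does not remove the point here, because the article states a general rule without exception and that rule does not suit these outcomes.

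Other limits stand. These outcomes are mostly secondary; the primary is change in PTSD symptoms. Cut-off distortion shrinks as the correlation rises. The error rates are for single tests at 5%, whereas the plan applies Holm–Bonferroni; that correction would not remove the bias, but the figures are not the planned tests' own error rates.

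**Conclusion.** The point holds in a conditional form. As written, a single EM fill is the only rule for missing values. None of the ways of applying it to the yes/no outcomes classifies missing women soundly; where a rate comes out near the truth, as with a cut-off at 50%, this is a coincidence of location and the test can still be invalid.

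For reabuse, the share of missing women coded present can lie anywhere from about 0% to 99% at assumed true rates of 10–30%, depending on order and threshold. The direction of any spurious arm difference is therefore unknown in advance. For cut-off outcomes, the average shift is moderate (30% to about 23–28%), and the inflated test size of about 8–26% requires arm in the fill model. All sizes scale with the share of missing assessments and would be smaller than shown if women who leave treatment are still assessed. This should be changed, but it does not threaten the primary comparison of continuous scores.

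**What to change.** State in the Statistical analysis section that yes/no outcomes (reabuse, cut-off improvement, presence of problems, success or failure) are not derived from single EM-filled scores. Replace that step as follows:

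- Use multiple imputation with arm in the model. Either draw full random scores and apply the presence rule or cut-off within each imputed data set, or impute the yes/no item by logistic regression.
- Combine the results with Rubin's rules.
- Fix the definition of presence for each type of violence.
- Add best-case and worst-case sensitivity analyses by arm, for reabuse as well as recovery. Scoring every unassessed woman as a failure is not enough alone, because dropout then reads as failure.

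One caution: with 30% missing and a true rate of 20%, only about 45 × 0.7 × 0.2 = 6 events per arm would be observed. Separate logistic models by arm would be unstable; use a penalised model, or one pooled across arms with an arm term.

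The cost is revised wording, a little more programming and somewhat wider standard errors. No new data or participants are needed.
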